This study was initiated to assess whether a period of 1 week of brace immobilisation within non- or minimally displaced DRFs is safe and will lead to an equal functional outcome, earlier return to work, higher patient satisfaction and reduction of health care costs compared to 3 weeks of cast immobilisation. The hypothesis of the study is that 1 week of brace immobilisation is non-inferior to 3 weeks of cast immobilisation.

This randomised controlled trial will provide level 1 evidence on the optimal period and way of immobilisation for non- or minimally displaced distal radius fractures in adult patients. Literature indicates that a shorter period of immobilisation and immobilisation by bracing is safe and might even be beneficial.

This study protocol is based on the ‘DR PIP II: Distal Radius Plaster Immobilization Period II’ study protocol (NL62861.029.17) where 4 weeks versus 6 weeks of cast immobilisation is analysed within displaced and reduced DRFs [21].

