### Sample size calculation

The primary outcome will be the PRWE score at 6-month follow-up, of which the minimal clinically important difference is 11.5 points. To be conservative, we use a non-inferiority limit of 10.0. The SD of the PRWE is 14.0 [35]. With a power (1 − *β*) of 90% and a type I error (*α*) of 5%, a sample size of 34 patients per treatment group was calculated.

To allow a 10% drop-out, 74 patients will be included, 37 patients per treatment arm. We expect that all patients can be included within 1–1.5 year.

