### Statistical analysis

Data from the demographic data collection and the outcome parameters will be cleaned blindly from the treatment data. Data are presented as mean scores with 95% confidence intervals. Linear regression analysis will be performed if data are not normally distributed.

A blinded evaluation of the trial patient’s functional status will be performed by a research assistant by use of the PRWE and qDASH scores. Blinded radiographic evaluation will be performed the intervention group and the control group. An independent expert will assess the degree of dislocation on an X-ray, blinded from the first assessment. Final blinded analysis of the primary outcome parameters will only be performed after 6-month follow-up.

The analysis of this study will be carried out according to the intention-to-treat principle, i.e. the patients will remain in the group they will be randomly allocated to at the baseline. Analysis of functional outcome will be assessed using repeated-measures analysis of variance (GLM 4) with the time as the within-group factor and the treatment as the between-group factor. The post hoc analysis will be performed on the time of randomisation. Group comparisons at different time points will only be made when the overall repeated-measures tests are statistically significant. All scores will be tested for normality using the Kolmogorov–Smirnov test. Parametric variables will be compared using the Student’s *t*-test, while non-parametric and ordinal variables will be compared using the Mann–Whitney *U* statistic. Nominal variables will be compared across independent groups using the chi-squared test or Fisher’s exact test. Homogeneity of variance will be assessed using Levene’s test.

Baseline characteristics that will be analyses are gender, age, dominancy, fracture side, fracture characteristics, smoking and osteoporosis. The outcome will be tested for normality and according to the outcome mean or median baseline characteristics will be compared.

Primary and secondary outcome measures are functional outcome (PRWE and qDASH), return to work, range of motion, pain, radiological outcome, complications and cost-effectiveness.

Missing data of the PRWE and qDASH score during follow-up can be imputed using multiple imputation based on baseline characteristics

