The PRWE questionnaire will measure the primary outcome (PRWE after 6-month follow-up). In this questionnaire, pain and function are scored on a 0 to 10 scale. The total score can range between 0 and 100, with 0 being the best possible outcome and 100 the worst. The outcome will be tested for normality, and according to the outcome mean or median PRWE after 6 months will be calculated. The mean or median outcome after 6 months in the intervention group (e.g. 1 week of brace immobilisation) will be compared with the control group (e.g. 3 weeks of cast immobilisation). A *t*-test will be used to compare the different outcomes. A *p* value of < 0.05 will be taken as a threshold of statistical significance. To check for clinically relevant results, we will compare the outcomes between the two groups to check whether this difference will reach the minimal clinically important difference of the PRWE of 11.5. Different variables will be compared between the two treatment groups (e.g. 1 week of brace and 3 weeks of cast immobilisation groups). In addition, if possible, a multivariate analysis will be performed, to compare different secondary outcomes to the period of brace or cast immobilisation. Depending on the amount of missing data, we will impute outcomes using multiple imputation based on age, sex, smoking and fracture characteristics. For all analysis, SPSS statistical software (version 28.0) will be used, in which two-tailed *p* value < 0.05 will be considered significant.

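### The protocol conflicts on whether the primary 6-month PRWE comparison must first pass a significant repeated-measures test, a condition that works against a non-inferiority aim

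*Protocol article*

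**What the plan says.** All places are in the protocol article.

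- **Background:** "The hypothesis of the study is that 1 week of brace immobilisation is non-inferior to 3 weeks of cast immobilisation".
- **Sample size calculation:** "The primary outcome will be the PRWE score at 6-month follow-up". The margin follows: "To be conservative, we use a non-inferiority limit of 10.0".
- **Statistical analysis, repeated-measures paragraph:** functional outcome is analysed by repeated-measures ANOVA "with the time as the within-group factor and the treatment as the between-group factor". After a sentence on post hoc analysis comes the condition: "Group comparisons at different time points will only be made when the overall repeated-measures tests are statistically significant". The section does not say which term of the model is the overall test.
- **Statistical analysis, list of outcomes:** "Primary and secondary outcome measures are functional outcome (PRWE and qDASH" heads the list, so the condition covers the instrument that carries the primary outcome.
- **Statistical analysis, paragraph on the primary outcome:** "The mean or median outcome after 6 months in the intervention group" is to be compared with the control group by t-test, with a two-tailed threshold of 0.05. This paragraph neither repeats the condition nor waives it.

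**The concern.** The primary outcome is a group comparison at one time point. Read literally, the repeated-measures paragraph allows that comparison only after an overall test has been significant. Such a condition suits a superiority trial that wants to limit testing at many time points. Here the aim is to show that the brace is not relevantly worse, and the result hoped for may well be two similar arms. The condition then asks for evidence that the arms differ before allowing the analysis meant to show that they do not differ by much.

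At stake is whether the trial reports its primary result at all. With two rules in the text, an analyst could stop under one or go on under the other, and could choose after seeing the data.

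**Working it through.** **Inputs from the protocol.** Margin 10.0, SD 14.0, power 90%, type I error 5% (sidedness not stated), 34 evaluable patients per arm, 37 per arm recruited, tests at two-sided 0.05.

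**Assumptions not in the protocol.** Within-patient correlation 0.3, 0.5 or 0.7 with compound symmetry. SD 14 at every time point. Two time points (6 weeks, 6 months) or three (adding the emergency department baseline). Illustrative time means of 60, 30 and 15, or 30 and 15 with two time points.

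**Step 1: the plan's own figure.** With no true difference,

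n per arm = 2 × SD² × (z₁₋α + z₁₋β)² / margin²

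- One-sided 5%: 2 × 196 × (1.645 + 1.282)² / 100 = 33.6, so **34**. This matches the protocol.
- One-sided 2.5%: 2 × 196 × (1.960 + 1.282)² / 100 = 41.2, so 42.

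The stated 90% power therefore belongs to an ungated, one-sided 5% non-inferiority test.

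**Step 2: how often the gate opens with equal arms.** A single test at 0.05 is significant in 5% of trials by construction. If either of two nearly independent tests suffices, the rate is 1 − 0.95² = 9.75%. A simulation of 10,000 trials per scenario (34 or 37 per arm, two or three time points, all three correlations) agrees:

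| Test that opens the gate | Comparison made | Comparison made and non-inferiority shown |
|---|---|---|
| No gate | 100% | 90–92% |
| Treatment effect | about 5% | about 3–4% |
| Treatment-by-time | about 5% | about 3–5% |
| Either of the two | 9–10% | 6–7% |
| Both required | 0.2–0.3% | not tabulated |
| Time effect also counts | about 100% | as with no gate |

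Non-inferiority here means that the upper one-sided 95% limit for brace minus cast lies below 10. With a one-sided 97.5% limit, the ungated rate is about 83% at 34 per arm.

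**Step 3: equal at 6 months, brace better at 6 weeks.** 34 per arm, three time points, gate opened by either test; ranges are over correlations 0.3 to 0.7.

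| Brace benefit at 6 weeks | Comparison made | Made and non-inferiority shown |
|---|---|---|
| 5 points | 30–52% | 25–45% |
| 10 points | 79–98% | 70–88% |

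The 6-month truth is the same in both rows. Only the 6-week difference changes whether the primary comparison is made.

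**Step 4: false non-inferiority claims.** A claim under the gate needs both an open gate and a successful test, so it cannot be more likely than the test alone. With the brace truly 10 points worse at 6 months only (34 per arm, three time points, correlation 0.5), the one-sided 5% test claims non-inferiority in 5.2% of trials without the gate and 2.5% with it.

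**The case against.** The strongest case on the other side has four parts.

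1. **The primary outcome has its own paragraph, with a named test and no condition.** The gate follows a sentence on post hoc analysis and speaks of several time points, so it may be meant only for contrasts within the repeated-measures model. On that reading the specific text governs and the t-test goes ahead. This is plausible, and the sponsor may not have meant to gate the primary comparison. But no sentence ranks one paragraph above the other or exempts the 6-month PRWE, so the conflict stands.
2. **The overall test is undefined.** If the time effect counts, recovery after a fracture would open the gate in practically every trial. That removes the harm, but also any purpose of the rule.
3. **Non-inferiority does not mean equality at every time point.** The hypothesis also covers a better brace arm, and the Background anticipates faster recovery with shorter immobilisation. At 6 weeks the brace arm has been free for about 5 weeks and the cast arm for about 3. This stands. A reader might infer that the primary comparison would almost never be made whenever the hypothesis is true. The documents do not support that: it needs the gate to apply to the primary outcome, the time effect not to count, and the arms to be equal throughout.
4. **The gate does not inflate error.** A reader might also infer that conditional testing raises the risk of a false non-inferiority claim. Step 4 shows that it cannot.

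**Conclusion.** The protocol gives two incompatible rules for its primary comparison, and one of them runs against the trial's aim. That much rests on the text alone.

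The size depends on the reading. If the gate applies and is opened by the treatment or treatment-by-time test, arms equal at all time points leave the comparison made in about 5 to 10% of trials, and power falls from about 90% to about 3 to 7%. The 5% for a single test is simply its significance level; the rest rests on the assumed correlation structure and number of time points. With an early brace benefit the loss is smaller, but the primary comparison then depends on a secondary time point. If the time effect counts, the gate has no effect. On none of these readings does the gate serve the primary comparison.

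The cost is lost power and a primary estimate reported only in selected trials. Deleting the gate would not by itself give a non-inferiority analysis, because the t-test described is a two-tailed test for a difference and makes no use of the 10.0 limit.

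**What to change.** Amend the Statistical analysis section to state that:

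- the 6-month PRWE comparison is the primary analysis and is made whatever the repeated-measures tests show;
- non-inferiority is judged by the confidence interval for the brace-minus-cast difference against the 10.0 limit, with the confidence level given (34 per arm corresponds to one-sided 5%; a two-sided 95% interval would have about 83% power at that size);
- the repeated-measures analysis, and any gate, apply to secondary comparisons only, and the model term that opens the gate is named.

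This takes a few sentences, with no extra patients, visits or data. It should be settled before anyone sees outcome data by arm.

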Patients can only participate if the DRF is non- or minimally displaced. They will receive written information and an informed consent form from the attending physician/the clinical investigator/research assistant. When the X-ray taken at the ED showed non- or minimal displacement, informed consent will be signed and eligible patients will be randomised (Fig. 1). An independent research assistant will perform a concealed permuted block randomisation by using a secured computer-generated randomisation schedule after stratification for gender and age. Allocation will be at random in four blocks (Table 1). In total, 1 week of brace immobilisation, if assigned to the intervention group, or 3 weeks of cast immobilisation, if assigned to the control group, will be executed. It is expected that all patients can be included within 1–1.5 year from the start of the study.

**Table 1 Tab1:** Stratification by gender and age

Patient characteristics			Randomisation
List 1	Male	< 30 y.o.a	ABAB AABB ABBA BABA BAAB
List 2	Male	> 30 y.o.a	BAAB BBAA ABAB AABB ABBA
List 3	Female	< 30 y.o.a	AABB ABBA BAAB BBAA BABA
List 4	Female	> 30 y.o.a	ABBA BABA ABAB AABB AABB

*y.o.a.* years of age, *A* 1 week of brace immobilisation, *B* 3 weeks of cast immobilisation

The inclusion and follow-up schedule are visualised in Fig. 2 and Table 2. All patients will be followed for 6 months in total. Assessments will occur at the time of admission at the ED, assessment by phone consult in 1 week after trauma (5–9-day window) in case of inclusion in the intervention group (e.g. 1 week of brace immobilisation), physical assessment in case of the control group (e.g. 3 weeks of cast immobilisation) at 1 (5–9-day window) and 3 weeks (18–24-day window). All patients will be physically assessed at 6 weeks (5–7-week window) and 6 months (5–7-month window) after the start of treatment. After removal of the brace or cast, additional physiotherapy is advised and exercises to train wrist function will be given.

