**Table 2 Tab2:**
[figure not shown]
SPIRIT figure

At each follow-up (FU) visit, the research coordinator or research assistant will ascertain patient status (i.e. secondary interventions, adverse events/complications, deaths) and will verify the information within medical records. All adverse events will be addressed to the principal investigator. The patients will be asked to indicate the actual pain level based on the VAS score, if they are currently treated by a physical therapist and if they returned to work. At 6 weeks and 6 months, the range of motion of the wrist will be measured using a goniometer.

Patients will be asked to complete questionnaires relating to disability (qDASH score and PRWE score) and medical consumption, productivity and general health to analyse cost-effectiveness (EQ-5D, iPCQ, iMCQ). Patients will be asked to complete the questionnaires at the ED as well, to generate baseline data.

Plain X-rays of the wrist will be made at the time of presentation in the hospital at the ED, after 6 weeks and 6 months. The X-ray at 6 months will be taken to determine the grade of degenerative joint changes. Time to define the presence of a delayed- or malunion will be at 6 months. Intention-to-treat principle will be maintained.

Both treatment options and used methods of treatment for this type of fracture are well known. Earlier research did not report any (serious) adverse events. All adverse events will be reported by the investigator; severe adverse events will be reported by the investigator to the sponsor of the study without undue delay after obtaining knowledge of the events. We performed an investigator-initiated risk classification: the risk of this study is expected to be negligible. Therefore, no DSMB/safety committee would be necessary. A monitoring audit will be conducted at the start of the study, after inclusion of the first 10 patients and after finishing the inclusion of patients. Also, a line listing of (serious) adverse events will be kept up and reported annually to the Amsterdam UMC Ethical Board.

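### The 6-month PRWE comparison is an unadjusted t-test although randomisation is stratified by gender and age and PRWE appears to be collected at the ED: a possible loss of precision, not a bias

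*Protocol article*

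**What the plan says.** - **Randomisation.** Sample and selection criteria describes concealed permuted blocks from a "randomisation schedule after stratification for gender and age". Table 1 gives four lists: male or female, below or above 30 years.
- **Baseline.** The follow-up text after Table 2 names the qDASH, PRWE and health-economic questionnaires and adds: "Patients will be asked to complete the questionnaires at the ED as well, to generate baseline data". Read plainly, that includes PRWE.
- **Primary comparison.** Statistical analysis sets "The mean or median outcome after 6 months in the intervention group" against the control group and names a t-test. No covariate is mentioned.
- **Other analyses of function.** The same section plans a repeated-measures ANOVA with time and treatment as its only factors. Age and sex enter the outcome analysis only through possible multiple imputation. A multivariate analysis is mentioned, if possible, for secondary outcomes.
- **Sample size.** "The primary outcome will be the PRWE score at 6-month follow-up"; "To be conservative, we use a non-inferiority limit of 10.0"; "The SD of the PRWE is 14.0". With 90% power and 5% type I error, the article arrives at 34 per arm, raised to 37 for drop-out.

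**The concern.** Stratified blocks hold the arms close to balance on gender and age. The difference in means therefore varies less from one randomisation to another than it would under simple randomisation, to the extent that those factors predict the outcome. A two-sample t-test takes no account of this: whatever variance the strata explain stays in its error term. The reported standard error is then larger than the true one, and the interval is wider than the design requires.

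Baseline PRWE is a different matter. It was not used to allocate patients, so omitting it leaves the t-test interval valid. All that is lost is whatever precision the baseline score could have added.

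In a non-inferiority trial the conclusion turns on whether the upper confidence limit lies below the margin. An interval wider than necessary raises the chance of failing to show non-inferiority when it is true. With about 34 evaluable patients per arm, it is worth asking how much precision is at stake.

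**Working it through.** **Inputs from the article (Sample size calculation):** margin 10.0, SD 14.0, power 90%, α 5% (sidedness not stated), 34 per arm. **Assumptions:** true difference 0; joint R² of gender, age stratum and baseline PRWE with 6-month PRWE between 0 and 0.30. The article gives no correlation, so the range is illustrative.

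**1. Reproduce the stated sample size.**

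n per arm = 2 × SD² × (z₁₋α + z₁₋β)² / margin²

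- One-sided 5%: 2 × 196 × (1.645 + 1.282)² / 100 = 33.57, rounded up to 34. This matches.
- One-sided 2.5%: 2 × 196 × (1.960 + 1.282)² / 100 = 41.19, rounded up to 42. This does not match.

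The 34 therefore rests on the full SD of 14.0, with no allowance for covariates. At one-sided 5% the unadjusted comparison has 90.3% power (normal approximation; 89.8% by noncentral t).

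**2. Unadjusted precision.**

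SE = 14 × √(2/34) = 3.395. With 66 degrees of freedom, t₀.₉₇₅ = 1.997, so the 95% CI half-width is 1.997 × 3.395 = 6.78 points.

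**3. Precision after adjustment.**

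Residual SD = 14 × √(1 − R²). The model has five coefficients (intercept, arm, gender, age stratum, baseline), leaving 68 − 5 = 63 degrees of freedom and t₀.₉₇₅ = 1.998.

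| Assumed R² | Residual SD | SE | 95% CI half-width | Power, one-sided 5% (noncentral t) |
|---|---|---|---|---|
| 0 | 14.00 | 3.395 | 6.79 | 89.8% |
| 0.10 | 13.28 | 3.221 | 6.44 | 92.3% |
| 0.20 | 12.52 | 3.037 | 6.07 | 94.7% |
| 0.30 | 11.71 | 2.841 | 5.68 | 96.7% |

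The ratio √(1 − R²) is 0.949, 0.894 and 0.837, so the SE falls by about 5%, 11% and 16%. At R² = 0 nothing is gained, and the loss of 3 degrees of freedom is hardly visible.

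**4. Simulation under the stratified design.** 68 patients in four strata, permuted blocks of 4, 5,000 replicates per scenario; t-test against a linear model with strata and baseline.

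| Variance explained: strata / baseline | Coverage of t-test 95% CI | Half-width: t-test | Half-width: adjusted |
|---|---|---|---|
| 0 / 0 | 95.3% | 6.74 | 6.81 |
| 5% / 0 | 95.3% | 6.75 | 6.65 |
| 10% / 0 | 95.8% | 6.77 | 6.47 |
| 10% / 20% | 96.2% | 6.77 | 5.71 |

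Coverage of the t-test interval is at or slightly above 95% throughout: the test is mildly conservative when the strata are prognostic and never anti-conservative here. If only the strata matter, and modestly, adjustment narrows the half-width by 0.1 to 0.3 points. Larger gains need a prognostic baseline score.

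**The case against.** **The trial was sized for an unadjusted comparison.** A reader might infer that the interval is too wide for the trial to reach its planned power. The article does not support that. The 34 per arm uses the unadjusted SD, and step 1 shows that it delivers about 90% power at one-sided 5% without any adjustment. This objection stands.

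**The power shortfall has another source.** A reader might start from 82.7% power (noncentral t, one-sided 2.5%, 34 per arm) and present adjustment as the remedy. That figure arises because the sample size matches only a one-sided 5% test, while Statistical analysis states that a two-tailed p "value < 0.05 will be considered significant". The mismatch is a separate issue. Adjustment may offset some of its effect but does not resolve it, and the shortfall should not be counted here.

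**The gain may be nil.** No correlation is given for gender, age or baseline PRWE. The ED score would be taken around the acute injury, and patients with pre-existing wrist deficits are excluded. A rating of the pre-injury wrist would probably vary little, and a rating of the acute wrist may say little about 6 months. The collection itself is not beyond doubt: the list of outcomes gives PRWE only at 6 weeks and 6 months, the day-of-trauma statement in Methods/design concerns the health-economic questionnaires, and the schedule in Table 2 is not shown. This stands as a limit on size and on the certainty of the baseline term. The case for the stratification factors does not depend on it.

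**The plan does not ignore these variables altogether.** The repeated-measures ANOVA might include an ED score as a time level, and imputation may use age and sex. That is correct, but neither adjusts the 6-month comparison for strata or baseline.

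**An unadjusted analysis is legitimate, and covariates are often left to the SAP.** It is legitimate. But the article names the test for the primary endpoint, so the point concerns a stated choice rather than a missing detail.

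**Conclusion.** The point holds as a matter of efficiency. The stated t-test does not use the factors on which patients are stratified. If those factors are prognostic, its standard error is somewhat too large; if baseline PRWE is prognostic, leaving it out costs further precision without making the interval invalid. There is no bias and no added risk of a false claim of non-inferiority.

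The size is conditional. With 34 per arm and SD 14.0, the 95% CI half-width goes from about 6.8 points (R² = 0) to about 6.4, 6.1 and 5.7 for R² of 0.10, 0.20 and 0.30, all assumed values. The absence of covariates from the stated comparison is certain; the benefit of adding them is not. The change is worth making because it costs little and lets the analysis follow the randomisation, not because the planned sample size fails without it.

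**What to change.** Before unblinding, state in the analysis text that:

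- the primary estimate is the treatment coefficient from a linear model of 6-month PRWE on arm, gender and age stratum (as used for randomisation), plus baseline PRWE where it is collected at the ED;
- its confidence interval is compared with the 10.0 limit;
- the unadjusted difference with its confidence interval is reported as a sensitivity analysis.

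Confirm first that PRWE is among the ED questionnaires and which state of the wrist it refers to. If it is not collected, the model keeps arm, gender and age stratum.

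The cost is a sentence or two of analysis text. Gender and age are needed for randomisation anyway, so no new data are required for them. If none of the covariates is prognostic, the loss is about 3 degrees of freedom (simulated half-width 6.81 instead of 6.74). The sidedness of α needs its own correction and should not be treated as settled by this change.

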## Methods/design

The aim of this trial is to evaluate the non-inferiority of 1 week of brace immobilisation in patients with non- or minimally displaced distal radius fractures. As the ideal treatment of DRF is short, safe and will lead to an early return to work or daily activities, non-inferiority of 1 week of brace immobilisation will be considered superior to a longer period of immobilisation. This hypothesis was also supported by the previous study performed by this study group [22].

Primary outcome is:

Patient-reported outcome measured by the PRWE score after 6 months

Secondary outcomes:

Patient-reported outcome measured by the Quick Disabilities of the Arm, Shoulder and Hand score (qDASH) after 6 weeks and 6 monthsPatient-reported outcome measured by the PRWE score after 6 weeksRange of motion after 6 weeks and 6 monthsPatient-reported pain score (VAS score) at arrival at ED, after cast/brace is applied, in the first week after brace/cast removal, at 6 weeks and 6 monthsRadiological outcome at 6 weeks and 6 monthsComplicationsCost-effectiveness measured by EQ-5D, iMCQ and iPCQ questionnaires

The PRWE is a validated 15-item (scored 1–10) self-reported questionnaire and is the best questionnaire for evaluating the patient-reported outcome in case of DRFs [23, 24]. Patients rate their outcome on a 0–10 scale on pain and functional outcome, and scores will be transformed to a 0–100 score. A higher score indicates greater disability. The DASH Outcome Measure is a validated 30-item self-reported questionnaire for patients with disorders of the arm, shoulder and hand [25, 26]. The QuickDASH (qDASH) is the shortened version of the DASH Outcome Measure, using 11 items instead of 30 (scored 1–5) to measure pain and functional outcome. At least 10 of the 11 items must be completed to calculate a score. The scores will be transformed to a 0–100. A higher score indicates greater disability.

Range of motion will be measured by using a goniometer: volar/dorsal flexion, radial/ulnar deviation and pronation/supination will be determined. Patient-reported pain score will be measured by using the VAS score. VAS score is a widely used method for pain assessments. Patients score their pain on a scale of 1–10. A higher score indicated a higher level of pain. The VAS score will be measured on the ED at arrival and after application of the brace of cast. Patients will also receive a dairy after cast removal to record their pain score.

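### The trial is sized for non-inferiority at a 10.0-point PRWE margin, but the stated primary analysis is a difference test plus a check against 11.5 and never uses that margin

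*Protocol article*

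**What the plan says.** **Hypothesis.** Background in the protocol article states: "The hypothesis of the study is that 1 week of brace immobilisation is non-inferior to 3 weeks of cast immobilisation".

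**Sizing.** Sample size calculation states: "The primary outcome will be the PRWE score at 6-month follow-up, of which the minimal clinically important difference is 11.5 points". It then chooses a stricter figure as the margin: "To be conservative, we use a non-inferiority limit of 10.0". The other inputs are "The SD of the PRWE is 14.0", 90% power and a type I error of 5% with no sidedness given. The result is 34 per arm, raised to 37 per arm (74 in total) for 10% drop-out.

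**Primary analysis.** Statistical analysis compares the 6-month mean or median PRWE between arms and names a t-test. A p "value of < 0.05 will be taken as a threshold of statistical significance", and the end of the section makes this two-tailed. For clinical relevance, the investigators will then "check whether this difference will reach the minimal clinically important difference of the PRWE of 11.5".

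**Other rules in the same section.** Functional outcome is also analysed by repeated-measures analysis of variance. Comparisons at single time points follow only if the overall test is significant. Confidence intervals of 95% are mentioned for presenting mean scores. The section ties no interval to 10.0 and gives no rule for concluding non-inferiority.

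**The concern.** A non-inferiority trial has to reject the hypothesis that the new treatment is worse by the margin or more. A t-test of equality addresses a different null hypothesis. A non-significant result may mean only that the trial is small, and a significant one does not say whether the difference exceeds the margin. Comparing an observed difference with 11.5 ignores sampling error. It also returns to the looser figure that the sample size section had set aside in order to be conservative.

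The condition on time-point comparisons adds a second problem. The result that would support the brace is two similar arms, and that is when an overall test is least likely to be significant. If the condition covers the PRWE, the 6-month comparison could be ruled out in the case where it matters most.

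At stake is whether the trial can answer its stated hypothesis, and whether a brace that is worse by the full margin could be reported as not different or not clinically relevant.

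**Working it through.** **Inputs** (Sample size calculation): margin 10.0, SD 14.0, power 90%, α 5%, 34 evaluable per arm. The values 11.5 and two-tailed 0.05 come from Statistical analysis. PRWE is higher when worse, so the difference is brace minus cast. A common SD and approximate normality are assumed.

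**1. Reproduce the plan's sample size.** For a true difference of zero, n per arm = 2 × SD² × (z₁₋α + z₁₋β)² / margin².
- One-sided 5%: 2 × 14² × (1.645 + 1.282)² / 10² = 33.6, so 34. This matches the plan.
- One-sided 2.5% (two-sided 95% interval): 2 × 14² × (1.960 + 1.282)² / 10² = 41.2, so 42. This does not match.

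The sample size is therefore a one-sided 5% non-inferiority calculation against 10.0. The fault lies in the analysis text.

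**2. Precision.** SE = 14 × √(2/34) = 3.40. With 66 degrees of freedom the critical values are 1.997 (two-sided 5%) and 1.668 (one-sided 5%).
- 95% half-width: 1.997 × 3.395 = 6.78.
- 90% half-width: 1.668 × 3.395 = 5.66.

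**3. If the brace is truly 10 points worse.** The non-centrality is 10 / 3.395 = 2.945.

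| Reading applied to the result | Chance of wrongly calling the brace non-inferior |
|---|---|
| p ≥ 0.05 read as non-inferior | 17.3% (non-central t; 17.2% in 100,000 simulated trials) |
| Observed difference below 11.5 read as non-inferior | Φ((11.5 − 10) / 3.395) = Φ(0.44) = 67.1% |
| Upper limit of two-sided 90% interval below 10.0 | 5% |
| Upper limit of two-sided 95% interval below 10.0 | 2.5% |

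With all 37 per arm, the first two rows become about 14% and 68%.

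**4. Where the rules disagree (34 per arm, observed SD 14).**
- The difference test is non-significant for observed differences up to 6.78. At that value the upper 95% limit is 6.78 + 6.78 = 13.56, beyond both 10.0 and 11.5.
- The margin test passes only below 10 − 5.66 = 4.34 (90% interval) or 10 − 6.78 = 3.22 (95% interval).
- Observed differences from 4.34 (or 3.22) up to 6.78 are thus non-significant yet fail non-inferiority.

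**5. Power of a margin-based rule at zero true difference, 34 per arm.** The one-sided 5% rule gives about 90%. The two-sided 95% interval gives about 83% (83.8% by the normal approximation).

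**The case against.** **The rates rest on readings that the article does not prescribe.** It introduces 11.5 as a check of clinical relevance, not as the criterion for non-inferiority, and it nowhere says that p ≥ 0.05 means non-inferior. This stands. The 17% and 67% show what could follow from each reading. They are not the trial's type I error rate.

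**An article condenses the full protocol, and an analysis plan may hold the real rule.** This would answer a silent article. This one names a test, a significance level and a threshold, and all three belong to a difference trial. An unseen plan could repair that only by departing from the published text.

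**The overall-test condition may not apply to the primary outcome.** This is possible, because the paragraph on the 6-month PRWE does not repeat it. But the condition sits in the text on functional outcome, and the PRWE is listed as a functional outcome, so its scope needs stating.

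**Two stronger readings are tempting, and the documents do not support them.**
- A reader might infer a planned untested superiority claim from the sentence that "non-inferiority of 1 week of brace immobilisation will be considered superior to a longer period of immobilisation". In context, it follows the remark that the ideal treatment is short, safe and allows early return to work. The natural sense is that the shorter treatment is preferred if outcomes are no worse. The wording is loose but plans no superiority claim on the PRWE.
- A reader might fault the plan because "The analysis of this study will be carried out according to the intention-to-treat principle", with no per-protocol set. Naming intention-to-treat is not an error, supportive sets are commonly left to the analysis plan, and the article gives no adherence figure on which to judge dilution.

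**Conclusion.** The point holds as a mismatch between the hypothesis and margin on one side and the stated primary analysis on the other. The sample size is internally sound as a one-sided 5% test against 10.0, but the analysis section specifies a two-tailed difference test and a comparison with 11.5. Followed as written, it does not test non-inferiority, and the condition on time-point comparisons may stand in the way of the one comparison that would.

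If the brace were truly at the margin, the chance of a wrong conclusion could be about 17% or 67%, depending on the reading, against 5% or 2.5% for a margin-based rule. These figures assume 34 evaluable per arm, SD 14 in both arms and roughly normal data. That the margin goes unused depends on none of these assumptions. This must be fixed before analysis.

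**What to change.** 1. Replace the primary-outcome text with a rule such as: non-inferiority is concluded if the upper confidence limit for the mean 6-month PRWE difference (brace minus cast) is below 10.0.
2. State the confidence level. A one-sided 95% limit (the upper end of a two-sided 90% interval) matches the calculation behind 34 per arm and keeps power at about 90%. If a two-sided 95% interval is preferred, restate the power as about 83% at 34 per arm. Alternatively, raise the evaluable number to 42 per arm: 42 / 0.9 = 46.7, so 47 per arm and 94 in total, against 74 now.
3. Keep 11.5 as a descriptive benchmark only.
4. State that the primary 6-month comparison is made whatever the result of the overall repeated-measures test.

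**Cost.** With the one-sided 95% limit this is a wording amendment that needs no new data or patients. The two-sided 95% interval costs either about 7 percentage points of power or 20 more patients (94 − 74).
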